**Methods and design:**

Patients with histological proven rectal cancer staged T2N+ or T3 are randomized to receive either SCRT (25 Gy in five fractions of 5 Gy) plus TME-surgery within 5 days or RCT (50.4 Gy in 28 fractions of 1.8 Gy, continuous infusion 5-fluorouracil) plus TME-surgery 4–6 weeks later. All patients receive adjuvant chemotherapy (12 weeks continuous infusional 5-FU) and are followed up for 5 years. TME-quality is independently documented by the surgeon and the pathologist. Hypothesis of the study is that RCT is superior to SCRT in terms of local recurrence after five years. Secondary endpoints are overall survival, disease-free survival, complete resection rate (R0 resection), rate of sphincter saving resection, acute and late toxicity (radiation related side effects), and quality of life (including long term bowel function).

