### Study objectives

The study compares the value of the two most common preoperative therapy regimens in LARC in terms of local recurrence. The primary outcome measure is local recurrence after a follow up of five years. The secondary outcome measures are overall survival, disease-free survival and quality of life (including long term bowel function) after a median follow-up of five years. Further more, secondary endpoints are the complete resection rate (R0 resection) and the rate of sphincter saving resection, both analysed after surgery of the last patient recruited. Acute and late toxicity (radiation related side effects) will be observed after a median follow-up of five years.

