### Statistics

Local recurrence after five years follow up has been chosen as primary endpoint. Survival in the regarded treatment arms will be graphically demonstrated by using Kaplan-Meier estimates. Univariate Log-Rank tests as well as multivariate Cox' regression analyses will be conducted for the analysis of primary and secondary endpoints. The alteration of hazard ratios in time will be modelled [11]. Proving a two-sided hypothesis of differences between the treatment arms, the calculation of the sample size of the trial was based on expected local recurrence rates of 12% in the SCRT arm compared with 7% in the RCT arm, resulting in altogether 760 patients (Log-Rank-test, base time: 5 years, accrual time: 6 years, follow-up: 5 years, proportion loss to follow-up: 10% per arm, error of the 1^st ^kind: α = 5% two-sided, power = 80%). An interim analysis is planned after five years study time with an error of the 1^st ^kind = α_int _= 0.5% [12].

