### Adjuvant chemotherapy and follow-up

2–4 weeks after complete resection continuous 5-FU infusion therapy with 300 mg/m^2 ^BSA is applied for 12 weeks as far as there is no contraindication as serious impaired wound healing or anastomotic leakage. Toxicity will be evaluated during the chemotherapy and at follow-up.

Patients are included into a standardized follow-up program according to the guidelines of the Tumorzentrum Berlin. This includes follow-up visits at 3, 6, 12, 18 and 24 months after surgery, and then every year for a total of 5 years. Each visit includes physical examination, abdominal ultrasound, rectosigmoidoscopy and endorectal ultrasound (in case of sphincter saving surgery), CEA level as well as a chest X-ray every year. In addition, pelvic CT (or MRI) -scans are performed 3 months, 12 months, 24 and 36 months after surgery. Furthermore a complete colonoscopy is required 18 months, 36 months and 60 months post treatment.

Radiotherapy-related toxicities will be assessed during every visit using the LENT SOMA criteria.

Evaluation of quality of life is assessed by the EORTC QLQ D30 and QLQ D 38 questionnaire at time of randomisation, end of therapy, 3 and 6 months, 1 year, 3 years and 5 years after surgery.

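### The 760 patients reproduce only with 5 to 11 years of recurrence follow-up per patient; on the five-year follow-up described, power for 12% v 7% is about 60-67%, not 80%

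*Protocol article*

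**What the plan says.** The Statistics section of the protocol article bases the sample size on "expected local recurrence rates of 12% in the SCRT arm compared with 7% in the RCT arm, resulting in altogether 760 patients", with the parameters "Log-Rank-test, base time: 5 years, accrual time: 6 years, follow-up: 5 years, proportion loss to follow-up: 10% per arm", a two-sided 5% type I error and 80% power. The base time is the horizon to which the 12% and 7% refer. Accrual and follow-up are listed as separate quantities.

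The follow-up described for a patient is shorter than those parameters imply:

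- Study objectives: "The primary outcome measure is local recurrence after a follow up of five years". The Statistics section sets the primary endpoint at the same five years.
- Abstract, Methods and design: patients "are followed up for 5 years".
- Adjuvant chemotherapy and follow-up: "follow-up visits at 3, 6, 12, 18 and 24 months after surgery, and then every year for a total of 5 years". Pelvic imaging ends at 36 months and colonoscopy at 60 months. No recurrence assessment is scheduled later.
- Discussion: further follow-up is mentioned for long-term toxicity and overall survival, in case local control proves equal. It is not mentioned for local recurrence.

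**The concern.** A log-rank calculation with 6 years of accrual and 5 years of additional follow-up counts events over 5 to 11 years per patient, 8 years on average under even accrual. At a constant hazard and without loss, about 35% of the events it counts fall after a patient's fifth year. If recurrence is assessed and analysed only to year 5, those events do not contribute, and the stated power belongs to a different design from the one described.

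The power is also part of the trial's case. The Background and the abstract's Discussion present the larger sample as an advantage over other comparative trials, and the main Discussion expects the trial to settle the question of local control. With power well below 80%, a true difference of 12% v 7% would be missed about one time in three or more, and a null result could be taken as equal efficacy.

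**Working it through.** **Inputs (Statistics section).** Five-year recurrence 12% (SCRT) and 7% (RCT); N = 760; accrual 6 years; follow-up 5 years; loss 10% per arm; two-sided 5%; power 80%. **Assumed:** 1:1 allocation, exponential hazards, uniform accrual, and loss modelled as exponential with 10% lost by year 5 (alternative: 760 × 0.9 = 684 evaluable).

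**Hazards.** λ₁ = −ln(0.88)/5 = 0.02557; λ₂ = −ln(0.93)/5 = 0.01451; HR = 0.568; ln HR = −0.566. Loss rate η = −ln(0.90)/5 = 0.0211.

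**Events for 80% power.** (1.960 + 0.842)² = 7.849.
- Schoenfeld: 4 × 7.849 / 0.566² = 98.
- Freedman: 7.849 × (1.568/0.432)² = 103.

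**Step 1: reproduce 760 (follow-up 5 to 11 years).** With μ = λ + η, the event probability is P = (λ/μ) × [1 − (e^(−5μ) − e^(−11μ))/(6μ)]. This gives 0.1695 and 0.1005, mean 0.1350.
- Lachin-Foulkes: N = 2 × [1.960√(2φ(λ̄)) + 0.842√(φ(λ₁)+φ(λ₂))]² / (λ₁−λ₂)², where φ(λ) = λ²/P(λ) and λ̄ is the mean hazard. With φ(λ₁) = 0.00386, φ(λ₂) = 0.00210 and φ(λ̄) = 0.00296, N = **762**.
- Freedman: 103.2/0.1350 = **765**.
- Schoenfeld with loss applied as a divisor of 0.9: **742**.
- At N = 760: 760 × 0.1350 = **103 events**; power 80-82%.

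All three are within 3% of the stated 760, so this is very probably how it was obtained.

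**Step 2: the same formulas with each patient followed for at most 5 years.** P = (λ/μ) × [1 − e^(−5μ)] gives 0.1140 and 0.0665, mean 0.0903. Events at N = 760: 760 × 0.0903 = **68.6**.
- Schoenfeld power: Φ(√68.6 × 0.566/2 − 1.960) = Φ(0.385) = **65.0%**.
- Freedman power: Φ(√68.6 × 0.432/1.568 − 1.960) = Φ(0.324) = **62.7%**.
- Lachin-Foulkes power: **62.8%**; N for 80% = **1,141**.

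**Step 3: vary the loss handling and the formula (5-year cap).**

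| Case | Events at 760 | Power |
|---|---|---|
| No loss (760 × 0.095) | 72 | 65-67% |
| Exponential loss | 69 | 63-65% |
| 684 evaluable (684 × 0.095) | 65 | 60-63% |
| Two proportions, 380 per arm | n/a | 65.2% |
| Two proportions, 342 per arm | n/a | 60.7% |

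Even with no loss, the smallest two-sided log-rank sample size for 80% is 1,031 (Schoenfeld); Lachin-Foulkes gives 1,084. No two-sided variant tried recovers 760.

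**Step 4: what 760 can detect with the cap.** For 12% v 6% with exponential loss, power is 80% (Freedman, Lachin-Foulkes) to 83% (Schoenfeld).

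**Step 5: does longer follow-up secure 80%?** Keep 5 to 11 years and the same loss, but lower the hazard after year 5 in both arms, with the hazard ratio unchanged. Halved: about 86 events, power 72-75%. Quartered: about 77 events, power 68-70%.

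**The case against.** The strongest objection is that the cap is inferred. The article nowhere says that recurrence data are censored at year 5 or that patients then leave the trial. The visit schedule belongs to a regional follow-up programme. Kaplan-Meier, log-rank and Cox analyses can use all available time. Five years beside six years of accrual is ordinary wording for minimum follow-up after accrual closes, and the five-year endpoint could be read as the time of analysis. On that reading 760 is consistent with its inputs.

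This stands to a degree. A reader might infer that the protocol ends observation at year 5, so that later recurrences are lost for certain and power is exactly 63-65%. The text does not support that firmness. It does contain four statements that point to five years per patient and none that provides for later recurrence assessment, so the two sets of statements still have to be reconciled. They are stated figures that do not fit together, and the point does not rest on detail left to a fuller document.

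A reader might also infer that following everyone until five years after the last randomisation would by itself secure 80%. Step 5 shows that it would not if the late hazard falls. Deaths before local recurrence would reduce late events further.

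Finally, the secondary endpoints are read out "after a median follow-up of five years". A reader might count this as a further contradiction. It is a different analysis time for different endpoints and has no bearing on the power of 760.

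Two smaller points do not change the result. Visits are timed from surgery, so time from randomisation runs slightly past five years; 5.3 years in both arms with loss gives 65-67%. And although the constant hazard is an assumption, recurrences concentrated before year 5 would leave 760 short even with the longer follow-up.

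**Conclusion.** The concern holds in this form: the stated 80% power corresponds to 5 to 11 years of recurrence follow-up per patient (about 103 events), while the endpoint, abstract and visit schedule describe five years (about 65-72 events). On the design as described, power for 12% v 7% is about 63-65% with 10% exponential loss, and 60-67% across formulas and loss handling. About 1,084 (no loss) to 1,141 (10% loss) patients would be needed for 80% by the formula that reproduces 760. The result rests on exponential hazards, uniform accrual, equal allocation and the inference that recurrence is counted to year 5 only. The arithmetic is secure; that inference is well supported but not explicit.

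**What to change.** Reconcile the sample size inputs in the Statistics section with the follow-up schedule, and state which period counts for the primary analysis.

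If it is five years per patient, restate the figure, for example:

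> With 760 patients each followed for 5 years, about 69 local recurrences are expected, giving roughly 60-67% power for 12% v 7% (80% power for about 12% v 6%).

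The references to adequate power in the Background and the abstract should then be softened to match. This costs only wording and a less favourable number.

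If the sponsor intends to count every recurrence until 5 years after the last randomisation, say so in the endpoint definition and the follow-up section. Give the target of about 103 events, and state that 80% depends on a constant recurrence hazard and hazard ratio beyond year 5, with about 72-75% if the late hazard is halved. This costs recurrence status collection beyond year 5 for patients recruited early. Neither route adds patients, but only the first gives a power figure that does not depend on events after year 5. The analysis time of the secondary endpoints need not change for this point.

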### Randomisation and stratification

Randomisation is done centrally at the clinical trial office of the Charité Comprehensive Cancer Center, Charité, Berlin. During randomisation patients are stratified by centre, tumour location (below 3 cm, between 3 and 8 cm, or between 8 and 12 cm above dentate line), TN-stage (uT2N+, T3N0, T3N+), open vs. laparoscopic surgery, and the type of resection (abdominoperineal resection vs. low anterior resection) according to the surgeons evaluation prior to preoperative therapy. Minimization has been used to ensure a balanced distribution with respect to arms and strata [13].

### Patient selection

In order to be included in the trial, patients are required to be aged 18 years or over and to have

1. Karnofsky Index 80% or better

2. Histological proved diagnosis of rectal cancer (adeno- or mucinous carcinoma)

3. Primary rectal cancer:

3.1. Maximum 12 cm above dentate line (upper limit)

3.2. Staged T2N+ or T3N0 or T3N+ (by endorectal ultrasound or Computed Tomography [CT]/Magnetic Resonance Imaging [MRI] scan)

4. No evidence of metastatic disease as determined by chest X-ray and abdominal ultrasound (or CT-scan of chest and abdomen or other investigations such as Positron Emission Tomography [PET] scan or biopsy if required)

5. Adequate bone marrow function with platelets more than 100 × 10^9/l and neutrophils more than 2.0 × 10^9/l

6. Creatinine clearance more than 50 ml/min

7. Serum bilirubin less than 2.0 × Upper Limit of institutional Normal range (ULN)

8. Written informed consent is obtained prior to commencement of trial treatment.

Exclusion criteria are:

1. Rectal cancer other than adeno- or mucinous carcinoma

2. Previous or concurrent malignancies, with the exception of adequately treated basal cell carcinoma of the skin or in situ carcinoma of the cervix

3. Patients with locally advanced inoperable disease, such as T4-tumour

4. Presence of metastatic disease or recurrent rectal tumour

5. Any previous chemotherapy or radiotherapy, and any investigational treatment for rectal cancer

6. Concurrent uncontrolled medical conditions

7. Pregnancy or breast feeding

8. Clinically significant (i.e. active) cardiac disease (e.g. congestive heart failure, symptomatic coronary artery disease) or myocardial infarction within the last six months

9. Stenotic tumour which can not be passed by the colonoscope and pre-operative need of diverting stoma

10. Evidence of hereditary colorectal cancer (Hereditary Non-Polyposis Colorectal Cancer [HNPCC] and Familial Adenomatous Polyposis [FAP])

11. Medical or psychiatric conditions that compromise the patient's ability to give informed consent

### Preoperative therapy

Radiotherapy is performed according to the standardized protocol with CT-based 3D-conformal treatment planning. The clinical target volume includes the primary tumour, the mesorectal tissue including perirectal and presacral nodes, and internal iliac lymph nodes [14]. The reference dose is defined in accordance to the International Commission on Radiation Units and Measurement report 50/63. All patients are irradiated in a prone position on a belly board with a CT-planned three-field technique with megavoltage photons ≥ 6 MV. An individual field shielding is obligatory by using a multileaf collimator. SCRT consists of single doses of 5.0 Gy in five fractions within one week up to a total dose of 25 Gy. For RCT, standard fractions of 1.8 Gy/d are given 5 times a week up to a total dose of 50.4 Gy; concomitant chemotherapy consists of continuous 5-FU-infusion 225 mg per square meter per day.

Radiotherapy-related toxicities will be assessed using the NCI Common Toxicity Criteria (CTC). Toxicity will be evaluated weekly during the therapy and at follow-up 3 months, 6 months, 1 year, 2 years and 5 years after treatment by standard forms (LENT SOMA).

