### Surgery and histopathological analysis

Surgical resection has to be done within 5 days after SCRT or 5–6 weeks after the completion of RCT. The standard surgical procedure is total mesorectal excision (TME), for tumours located 10 cm above the anal verge a partial mesorectal excision (PME) is feasible; anterior resection, intersphincteric resection or abdominoperineal resection is done according to clinical staging and patient's preference. Quality (completeness) of TME has do be evaluated and documented by every surgeon at the resected specimen (by injection of methylene blue into the arteria rectalis superior).

The surgical specimens are processed and evaluated by standardized pathology and including UICC TNM categories and staging groups, number of examined and involved lymph nodes and the status of resection margins. In addition, the CRM (circumferential resection margin) and the TME-quality have to be documented by the pathologist according to the British Medical Research Council [15]. Histopathological response is deduced from tumour regression (TRG). TRG is evaluated according the 5 point scoring system of Dworak [16].

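### Weekly toxicity checks stop with the preoperative therapy, so scheduled acute assessments follow treatment length (1 v 5.6 weeks); the late schedule is stated in two conflicting ways

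*Protocol article*

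**What the plan says.** All references are to the Protocol article. The section Preoperative therapy sets the toxicity schedule: "Toxicity will be evaluated weekly during the therapy and at follow-up 3 months, 6 months, 1 year, 2 years and 5 years after treatment", on LENT SOMA forms. The same section fixes the length of each regimen. For the short course, "SCRT consists of single doses of 5.0 Gy in five fractions within one week up to a total dose of 25 Gy". For radiochemotherapy, "standard fractions of 1.8 Gy/d are given 5 times a week up to a total dose of 50.4 Gy", which the Abstract gives as "50.4 Gy in 28 fractions of 1.8 Gy, continuous infusion 5-fluorouracil".

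The section Surgery and histopathological analysis states: "Surgical resection has to be done within 5 days after SCRT or 5–6 weeks after the completion of RCT". The section Adjuvant chemotherapy and follow-up starts chemotherapy 2 to 4 weeks after complete resection unless contraindicated and adds: "Toxicity will be evaluated during the chemotherapy and at follow-up". It gives no frequency.

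That last section also sets a second late schedule. It says "Radiotherapy-related toxicities will be assessed during every visit using the LENT SOMA criteria", and the programme has "follow-up visits at 3, 6, 12, 18 and 24 months after surgery, and then every year for a total of 5 years".

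The Abstract and Study objectives name acute and late toxicity as secondary endpoints.

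**The concern.** An acute toxicity comparison between arms needs the same opportunity to record an event in each arm over the same stretch of time. Here the weekly assessments are tied to being on preoperative therapy, and that period is more than five times as long in one arm. A radiation effect that appears two to four weeks after the start meets a scheduled assessment with RCT. With SCRT it meets none until chemotherapy begins. The comparison then mixes true toxicity with how often patients were examined.

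The late schedule has a different defect. Two sections prescribe different assessment times and different time origins for what appears to be the same instrument and the same effects. Centres could follow either section and believe that they comply.

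**Working it through.** **Step 1: length of the weekly window.** The Abstract's fraction count is reproduced first: 50.4 Gy / 1.8 Gy = 28 fractions. At five a week, 28 / 5 = 5.6 weeks. For SCRT, 25 Gy / 5 Gy = 5 fractions, delivered within 1 week.

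**Step 2: both arms on one time axis.** Weeks are counted from the start of radiotherapy. Inputs are the intervals in Surgery and histopathological analysis (within 5 days; 5 to 6 weeks) and in Adjuvant chemotherapy and follow-up (2 to 4 weeks after resection; first visit 3 months, taken as 13 weeks, after surgery).

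| | SCRT | RCT |
|---|---|---|
| End of radiotherapy | 1.0 | 5.6 |
| Weekly assessments | about 1 | about 5 to 6 |
| Surgery | 1.0 to 1.0 + 5/7 = 1.7 | 5.6 + 5 = 10.6 to 5.6 + 6 = 11.6 |
| Start of chemotherapy | 1.0 + 2 = 3.0 to 1.7 + 4 = 5.7 | 10.6 + 2 = 12.6 to 11.6 + 4 = 15.6 |
| End of radiotherapy to chemotherapy | 2.0 to 4.7 | 7.0 to 10.0 |
| 3-month visit | 14.0 to 14.7 | 23.6 to 24.6 |

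The Abstract gives the RCT interval to surgery as 4 to 6 weeks, not 5 to 6. With that figure, the lower ends of the RCT entries from surgery onward fall by one week. The two statements of the interval also need to be reconciled.

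Two things follow. From week 1 to somewhere between weeks 3.0 and 5.7, SCRT has no stated assessment, while RCT is assessed weekly over almost all of that stretch. And the 3-month visit falls about ten weeks later in RCT than in SCRT, so it cannot mark the end of a common acute window.

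**Step 3: late schedules as sets of months.**

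- Preoperative therapy: 3, 6, 12, 24, 60 (five times), counted from treatment.
- Adjuvant chemotherapy and follow-up: 3, 6, 12, 18, 24, 36, 48, 60 (eight visits), counted from surgery.
- Only in the second list: 18, 36, 48. Only in the first list: none.

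If treatment means radiotherapy, the two origins differ by at most 5 days with SCRT and by 5 to 6 weeks (Abstract: 4 to 6) with RCT. Six weeks is 6/13 = 46% of a 3-month interval, 6/52 = 12% of one year and 6/260 = 2% of five years.

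**The case against.** The strongest reply is that the frequency on treatment is the same in both arms, once a week. The additional RCT assessments come from 4.6 more weeks of radiation with continuous 5-FU, which is real exposure. This stands in part: some of any RCT excess would be genuine. It does not supply a common window.

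Second, assessment does not cease after SCRT until 3 months, as a reader of Preoperative therapy alone might infer. Toxicity is also evaluated during adjuvant chemotherapy in both arms. The unassessed stretch between radiotherapy and chemotherapy is in fact longer with RCT (7 to 10 weeks against 2 to 4.7). Both facts stand and prevent a claim that every gap runs one way. They do not cover the weeks just after SCRT, and the chemotherapy assessments have no stated frequency and do not reach patients with a contraindication.

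Third, a reader might turn the number of assessments into a bias estimate by assuming a fixed chance of recording an event each time. The documents do not support that. They give no such chance, persistent effects make successive assessments dependent, and the calculation would count real exposure as ascertainment.

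Fourth, a reader might infer that the late conflict also makes the arms incomparable, or that it leaves three years unassessed between months 24 and 60. Both sections apply to both arms, and following the every-visit rule satisfies both lists of months. Only the time origin could differ by arm, and that matters little from the first year on.

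Fifth, a reader might infer that acute toxicity would decide between the regimens if local control is similar. The Discussion names only long-term toxicities, with overall survival, and says that they could help.

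Finally, a condensed article may leave window definitions and form schedules to the full protocol. Their absence is not the point here. The point rests on a weekly rule that the article states and on two late schedules that it states differently.

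**Conclusion.** The concern holds in two limited parts.

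Acute: scheduled assessments follow treatment length, 1.0 against 5.6 weeks, and the weeks just after SCRT have no stated assessment until chemotherapy. The comparison of a named secondary endpoint is therefore exposed to unequal ascertainment. For effects emerging within the RCT course the likely direction is more recorded toxicity with RCT. The size cannot be derived from the document, and part of any excess would be real. This assumes that the therapy in the weekly rule is the preoperative therapy, as the section heading indicates.

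Late: five against eight assessment times, with two time origins, in both arms alike. This is an ambiguity that may vary by centre and must be reconciled. It is not evidence of a biased arm comparison.

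The primary endpoint is untouched. The change is worth making because it is cheap and, with 476 of 760 patients enrolled at the time of the article, 760 − 476 = 284 were still to be recruited.

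**What to change.** **Acute toxicity.** Define the comparison as worst grade over one fixed number of weeks from randomisation or start of radiotherapy, the same in both arms and not ending at a visit timed from surgery. Keep the weekly assessments. In addition, complete the same form in both arms at contacts that already occur: surgical admission, discharge, and the start of and visits during adjuvant chemotherapy. Record the treatment phase on each form so that surgical and chemotherapy effects can be separated from radiation effects, because the arms reach surgery and chemotherapy at different weeks of the window.

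**Late toxicity.** Reconcile Preoperative therapy with Adjuvant chemotherapy and follow-up: one list of LENT SOMA times and one time origin. The every-visit list already contains all the months in the shorter list, so adopting it loses nothing.

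**Cost.** A few more forms per patient at existing contacts, and a wording change for the late schedule. Treatment does not change. The number of assessments within the window will still not be identical in the two arms, so the report should show how many were completed in each.
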